## Abstract

**Background: **Heart failure (HF) is a debilitating condition associated with enormous public health burden. Management of HF is complex as it requires care-coordination with different cadres of health care providers. We propose to develop a team based collaborative care model (CCM), facilitated by trained nurses, for management of HF with the support of mHealth and evaluate its acceptability and effectiveness in Indian setting.

**Methods: **The proposed study will use mixed-methods research. Formative qualitative research will identify barriers and facilitators for implementing CCM for the management of HF. Subsequently, a cluster randomised controlled trial (RCT) involving 22 centres (tertiary-care hospitals) and more than 1500 HF patients will be conducted to assess the efficacy of the CCM in improving the overall survival as well as days alive and out of hospital (DAOH) at two-years (CTRI/2021/11/037797). The DAOH will be calculated by subtracting days in hospital and days from death until end of study follow-up from the total follow-up time. Poisson regression with a robust variance estimate and an offset term to account for clustering will be employed in the analyses of DAOH. A rate ratio and its 95% confidence interval (CI) will be estimated. The scalability of the proposed intervention model will be assessed through economic analyses (cost-effectiveness) and the acceptability of the intervention at both the provider and patient level will be understood through both qualitative and quantitative process evaluation methods.

**Potential Impact:** The TIME-HF trial will provide evidence on whether a CCM with mHealth support is effective in improving the clinical outcomes of HF with reduced ejection fraction in India. The findings may change the practice of management of HF in low and middle-income countries.

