Caregivers of patients with HF	In-depth interview Total 10–12 IDIs	● Perceptions and behaviours on clinical management, lifestyle, and self-care ● Feedback on proposed intervention components and methods ● Gauge caregivers’ interest and acceptability
Physicians Nurses Dieticians Physiotherapists	In-depth interview 10–12 interviews in each category (30–36 total interviews)	● Perceived quality of HF care ● Perceived patient barriers and facilitators to delivery of care, lifestyle change, and self-care ● Gauge feasibility of planned intervention components

**
*Collaborative care model intervention (Aim 2)*
**

A parallel group cluster RCT of more than 1500 adult HF patients with reduced ejection fraction from 22 units in India
^
36
^ will be used to address Aim 2. Each participating unit will be randomly assigned to one of two arms: 1) those delivering a comprehensive CCM (intervention) or 2) those delivering standard of care (usual care).

The selected hospitals will be independent units with dedicated staff employed at each site for recruitment and follow-up of patients included in the trial. The site teams will have similar compositions in terms of clinical roles.

Cluster eligibility criteria: Eligible units will include HF centres of major hospitals from the national heart failure registry or Kerala heart failure registry that serve ≥80 new patients in six-months and consented to the randomisation plan. All HF patients will also be required to provide individual consent to participate in the study.

Patient eligibility criteria and randomisation: Potential participants must meet the standard definition of HF
^
37
^ (HF with reduced ejection fraction of <40%) based on echocardiography to be eligible to enter the study. Consecutive patients will be recruited from the participating centres. Eligible units will be randomised at one time point, prior to trial implementation. The allocation ratio will be 1:1. Randomisation procedures will not be blocked, restricted, or matched. We will use computer generated random numbers to allocate half of the units to each arm of the study.

*Duration of treatment period and follow-up*

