**Data analysis plan**

Aim1: All interviews conducted in local language (Malayalam) will be simultaneously translated to English and transcribed. Interviews conducted in English language will be transcribed. The data analysis will follow a framework method of analysis
^
55
^. After the data is transcribed, the transcripts will be read line-by-line to get familiarised with the data. First a few transcripts will be coded using an inductive method. Later, a working analytical framework will be generated by merging the initial codes. The working analytical framework will then be used to index the remaining interviews. After indexing all the interviews, key themes will be generated by merging categories having similar meaning for each stakeholder. Finally, the data will be interpreted based on the convergences and divergences between the data themes across different stakeholders.

 Aim 2: All quantitative analysis will follow guidelines of cluster randomised trials
^
56
^. We will employ intention to treat analysis except in the sub-group analyses. Initially, baseline characteristics will be compared by treatment group to examine the adequacy of randomisation. The primary analysis will be a complete case analysis. However, missing data on outcome variables will be reported and sensitivity analyses will be conducted after multiple imputation of missing data.

The DAOH will be calculated by subtracting days in hospital and days from death until end of study follow-up from the total follow-up time of 730 days. The DAOH is a patient-centred outcome, which accounts for multiple events over the two-year course of a study period, weighs death more than hospitalisation, and deaths occurring early more than those occurring later. Empirical density curves will be created to show the distribution of DAOH over two-year follow-up period, stratified by intervention group. The median and the interquartile range of DAOH by treatment group will be provided. Poisson regression with a robust variance estimate
^
57
^ and an offset term to account for clustering will be employed in the analyses of DAOH per two-years of follow-up time. This procedure will yield a rate ratio and 95% CI
^
57
^. The rate ratio is the DAOH in the intervention arm divided by DAOH in the enhanced usual care arm. A rate ratio of >1 indicates more DAOH in the intervention arm in comparison to the usual care arm (i.e., favours the intervention).

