Multilevel mixed-effects survival models will be employed for analyses of time to secondary outcomes (composite of mortality and hospitalisation). A random term identifying the location of participating sites will account for the clustering effect. We will also conduct a landmark analysis conditional upon intervention group membership at 30 days of follow-up. The between-group differences for each of the secondary outcomes (other than binary outcomes variables) will be measured using mixed-effect linear models and after accounting for clustering of observations. Standard errors will be calculated using robust estimation procedures
^
58
^.

Pre-specified sub-group analyses (age group, sex, region, type of facility, clinical severity) will be conducted. The significance of subgroup effects will be assessed by tests of interactions of covariates and the treatment effect.

Finally, as an exploratory analysis we will also use win ratio
^
59
^ to analyse the composite secondary outcome of mortality and hospital admissions. The win ratio statistic prioritises the mortality and hospitalisation endpoints through sequential comparisons. Patients in the intervention and usual care group will be converted into matched pairs based on their baseline risk profiles. The intervention patient will be labelled as a ‘winner’ or a ‘loser’ depending on who died first. If there is no death, the pairs will be labelled a ‘winner’ or ‘loser’ depending on who had a hospitalisation first. Otherwise, they are considered tied. Finally, the win ratio will be generated, which is the total number of winners divided by the total numbers of losers. A 95% confidence interval and
*P*-value for the win ratio will be obtained. If matched pairs are not possible; the analyses will be conducted on unmatched pairs.

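### The primary DAOH model assigns clustering to an offset, which cannot handle it, and does not state the level of its robust variance

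*Protocol article*

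**What the plan says.** Hospitals, not patients, are randomised: "Each participating unit will be randomly assigned to one of two arms" (Study design approach, Aim 2).

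For the primary outcome, the Data analysis plan (Aim 2) names "Poisson regression with a robust variance estimate" and then, in the same sentence after a citation, "and an offset term to account for clustering will be employed in the analyses of DAOH per two-years of follow-up time". The Abstract repeats this: "Poisson regression with a robust variance estimate and an offset term to account for clustering will be employed in the analyses of DAOH". DAOH is obtained by subtracting hospital days and days after death "from the total follow-up time of 730 days".

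Two other statements bear on the point. The Aim 2 analysis text opens with a general commitment: "All quantitative analysis will follow guidelines of cluster randomised trials". For the time-to-event secondary outcome a working device is named: "A random term identifying the location of participating sites will account for the clustering effect". The linear models for other secondary outcomes are also said to allow for clustering. For the primary model, the article names no hospital random effect, no GEE and no variance clustered on hospital.

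Trial sample size and power assumes 22 clusters (11 per arm), 770 patients per arm, an ICC of 0.01, a design effect of 2.08 and a cluster-size coefficient of variation (CV) of 0.85.

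**The concern.** The only device tied by the wording to clustering is one that cannot deal with it. An offset is a known term whose coefficient is fixed at 1. It sets the exposure and adds neither between-hospital variance nor within-hospital correlation. The robust variance might do the job, but only if it is computed over hospitals, and the text does not say so. Computed over patients, it corrects for wrong dispersion and leaves within-hospital correlation untouched.

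Two competent analysts could therefore follow this sentence and report materially different confidence intervals and p-values for the sole primary outcome. More hangs on that p-value than usual: a significant primary result triggers the lifetime economic evaluation, and the Abstract expects the findings may change practice. This is not detail merely left to an SAP, because the article names a mechanism and the mechanism is the wrong one.

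**Working it through.** **Inputs.** From Trial sample size and power: SD 69 days, DAOH 586 vs 566 (20 days, also described as 3% higher), 770 per arm, 11 clusters per arm, ICC 0.01, design effect (DE) 2.08, CV 0.85, two-sided 5% alpha, 91% power. From Study coordination: 70 patients per centre. From the Data analysis plan: 730 days for each patient.

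**1. The plan's own figures.** The standard error of the difference is 69 × √(2 × 2.08/770) = 5.07 days.
- With 3% of 566 = 16.98 days: power = Φ(16.98/5.07 − 1.96) = 91.7%, which matches the stated 91%.
- With 20 days: power = 97.6%, which does not match.

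For the design effect:
- Equal clusters: 1 + 69 × 0.01 = 1.69.
- CV 0.85: 1 + ((0.85² + 1) × 70 − 1) × 0.01 = 2.20, or 2.05 by the relative-efficiency formula.

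The stated 2.08 lies between the two CV-based values. The trial was plainly sized for clustering.

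**2. What the offset does.** With log 730 as offset, log μ = log 730 + β₀ + β₁x = (β₀ + log 730) + β₁x. Only the intercept moves. Fitting a Poisson model to simulated DAOH with and without this offset left the treatment log rate ratio unchanged, and also its standard error, whether computed over patients or over hospitals. An offset that varied between patients would still add no hospital-level variance.

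**3. If the robust variance is at patient level.** The standard error is too small by √2.08 = 1.44; that is, it is 1 − 1/1.44 ≈ 31% below its correct value. Type I error is 2 × (1 − Φ(1.96/√DE)):
- DE 1.69 (equal clusters): 1.96/1.30 = 1.51, giving 13.2%
- DE 2.08 (as stated): 1.96/1.44 = 1.36, giving 17.4%
- DE 2.20 (CV 0.85): 1.96/1.48 = 1.32, giving 18.6%

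**4. Simulation.** 20,000 null trials per setting, 22 clusters, mean size 70, ICC 0.01, normal outcomes with mean 566 and SD 69, and gamma-distributed sizes where the CV is 0.85. Rejection rates at nominal 5%:

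| Variance and reference | Equal clusters | CV 0.85 |
|---|---|---|
| Patient-level robust, normal | 13.2% | 18.0% |
| Clustered on hospital, normal, uncorrected | 7.6% | 10.4% |
| Clustered on hospital, 22/20 factor, t(20) | 5.0% | 7.3% |

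A left-skewed outcome at CV 0.85 gave 17.7%, 10.5% and 7.3% for the three rows. In a separate simulation at CV 0.85, the Mancl-DeRouen correction with t(20) gave 4.8%, the Kauermann-Carroll correction with t(20) 6.6%, and a t-test on cluster means 4.8%.

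**The case against.** A reader might infer that the primary test will be anti-conservative at about 17%. The document does not support that as an unconditional statement. The sentence contains a robust variance, its stated purpose is to deal with clustering, and the same section commits to cluster-trial guidelines. A marginal model with a variance clustered on hospital needs no random effect, so the absence of one proves nothing. A Poisson model on hospital totals, with log person-time as offset and a robust variance over hospitals, would also be sound, although there the aggregation does the work and not the offset. All of this stands, and it makes the consequence conditional. It does not repair the sentence: a general promise to follow guidelines does not tell an analyst which variance to compute when the specific text names the wrong tool.

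The size also depends on cluster-size variation. The article assumes a CV of 0.85, yet also describes equal clusters and 70 patients per centre, so both ends of the range belong in the account.

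The residual 7.6% to 10.4% under hospital clustering arises from having only 22 clusters, not from the offset. Which correction to use is a detail that an article may leave to the SAP.

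A reader might also extend the criticism to the secondary analyses. The text does not support this. The site random term in the survival model is a valid device, and the statement "Standard errors will be calculated using robust estimation procedures" follows a commitment to allow for clustering.

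**Conclusion.** The point holds as a wrongly stated method for the primary analysis. The offset cannot account for clustering, here it has no effect on the treatment comparison at all, and the level of the robust variance is left open. Confidence in that is high, because it follows from the wording and from algebra.

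The consequence depends on how the open part is read. Under the patient-level reading, a nominal 95% interval covers about 83% of the time at the stated design effect (100 − 17.4), and type I error spans about 13% to 18%. Under the hospital-level reading the main problem disappears and a small-sample excess remains unless it is corrected. These figures rest on the protocol's assumed ICC of 0.01. In the simulations, an ICC of 0.02 with patient-level variance gave 20.4% (equal clusters) to 27.5% (CV 0.85). Because this is the sole primary analysis and the remedy is a sentence, it should be corrected before outcome data are analysed.

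**What to change.** Replace the sentence in the Data analysis plan, and its counterpart in the Abstract, with wording such as: DAOH will be analysed by a log-link Poisson model (GEE or equivalent) with log follow-up time (730 days) as offset; the robust variance will be clustered on the 22 randomised hospitals, with a small-sample correction and a t reference distribution on 20 degrees of freedom. The particular correction can be named in the SAP. The simulations suggest choosing it with unequal cluster sizes in mind, since the simple 22/20 factor still gave 7.3% at CV 0.85.

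The cost is wording and a few lines of code. No data collection, recruitment or sample size needs to change. Confidence intervals become wider than a patient-level analysis would give, as the design requires. The t(20) reference also costs a little power: at design effect 2.08 it falls from 91.7% to about 88.9% for the 3% effect, and from 97.6% to about 96.3% for 20 days.

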Self-management Medication adherence, weight, family support, diet, depression care	Morisky, Green and Levine medication adherence scale ^ 42 ^, weight management ^ 38 ^, Diet Management ^ 38 ^, Family support ^ 38 ^; Patient care in depression ^ 38 ^
Quality of life	KCCQ ^ 43 ^, EQ-5D-5L ^ 44, 45 ^
Walking ability	6 Minute Walk Test ^ 46 ^
Physical disability (muscular strength)	Hand grip strength- Dynamometer
Frailty	Fried frailty index ^ 47, 48 ^
Functional capacity	Specific Activity Questionnaire ^ 38 ^
Physical activity intensity	The Borg Scale of Perceived Exertion ^ 49 ^
Disease severity	Modified Borg Dyspnea Scale during 6MWT (0 – 10) ^ 50, 51 ^, Responsiveness to change in heart failure symptoms ^ 38 ^
Treatment burden	MTBQ ^ 52 ^
Patient satisfaction	Patient satisfaction in Quality of care ^ 38 ^, Care transitions measure (CTM3) ^ caretransitions.org/ ^, B-Prepared Scale ^ 53 ^

PHQ-9- Patient Health Questionnaire- 9, GAD-7- Generalised Anxiety Disorder Questionnaire, KCCQ-Kansas City Cardiomyopathy Questionnaire, EQ-5D-5L -EuroQoL 5dimension -5 level ,6MWT- Six Minute Walk Test, MTBQ- Multi-morbidity Treatment Burden Questionnaire, ECHO -Echocardiogram, ECG -Electrocardiogram

Kansas City Cardiomyopathy Questionnaire (KCCQ)
^
43
^ and EQ-5D-5L
^
44
^ will be used to measure quality of life.

A standard adjustable handgrip dynamometer will be used to measure handgrip strength. Three measurements will be taken in dominant and non-dominant hand. The average of the highest value of dominant and non-dominant handgrip strength will be used in the analysis.

The six-minute walk test (6MWT) will be measured during the baseline and follow-up visits by following the standard protocol
^
46
^. Before the 6MWT, the research nurse will measure blood pressure, pulse, and oxygen saturation with the help of a pulse oximeter. During the test, participants will have to walk for six minutes. After the test, staff will record the distance covered along with oxygen level, pulse rate and post walk Borg dyspnoea levels.

Treatment burden will be assessed by using multimorbidity treatment burden questionnaire (MTBQ)
^
52
^. Health care expenditure data will be collected every six months using a treatment expenditure questionnaire
^
38

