**Trial sample size and power**

The mean difference in DAOH was assumed to be 20 days (586 Vs 566 days with a standard deviation of 69 days) at two-year. We used the DAOH at two-year from the Trivandrum Heart Failure Registry in the sample size calculation
^
7
^. In the intervention group, we assumed 3% higher DAOH. A sample size of 770 HF participants per group (a total of 1540), in 11 equal clusters per arm (total 22 clusters) provides 91% power for a 2-sided 5% alpha. Assumptions; an ICC of 0.01 (design effect 2.08), coefficient of variation of cluster size of 0.85.

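### Effect modification by age is planned on age groups; if the interaction test uses those groups, keeping age continuous would avoid a loss of about 36% of the information for a median split or 21% for tertiles scored as a trend

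*Protocol article*

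**What the plan says.** The Data analysis plan (Aim 2) of the protocol article lists five modifiers: "Pre-specified sub-group analyses (age group, sex, region, type of facility, clinical severity) will be conducted". It continues: "The significance of subgroup effects will be assessed by tests of interactions of covariates and the treatment effect".

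Age is therefore named as a grouped factor. The article gives neither the number of age groups nor the cut-points, and it does not state how the covariate is coded in the interaction model. Clinical severity is listed without a scale. Table 2 has a disease severity row with two entries, "Modified Borg Dyspnea Scale during 6MWT (0 – 10") and "Responsiveness to change in heart failure symptoms", but nothing links either to the sub-group analysis. Table 3 schedules the responsiveness item at follow-up only. The article claims no power or precision for any sub-group test.

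**The concern.** If age is cut into groups before the test, patients at opposite ends of one group are treated as identical, and neighbours on either side of a boundary as different. When benefit changes steadily with age, this discards information, and the answer then depends in part on where the boundaries fall.

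Only the main comparison of days alive and out of hospital (DAOH) has a power calculation, so interaction tests have no planned power to spare. Region and type of facility are features of the 22 hospitals. Age varies among patients within a hospital, so it is one of the modifiers the trial can study with some precision. At stake is a real age gradient being missed and reported as no evidence of effect modification.

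**Working it through.** **Figure in the plan.** There is none to reproduce for this point. The only stated power ("provides 91% power for a 2-sided 5% alpha") concerns the main comparison and is not used below. The article gives no size for an interaction, so the check is relative: what share of the information in a continuous-age test survives grouping?

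**Assumptions, none of them from the article.**
- Age in years is available from the baseline demographic data.
- Age is roughly normal, and the treatment effect changes roughly linearly with it.
- Clustering affects the continuous and the grouped test alike.
- The continuous test has 80% power at two-sided 5%, as a reference point only.

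**Formula.** For a standardised covariate, the information retained is the share of its variance that lies between groups, R = Σ pⱼμⱼ², where pⱼ is the proportion in group j and μⱼ its mean. For two groups split at quantile q with normal cut-point c, this is R = φ(c)² / [q(1 − q)].

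**Median split.** φ(0) = 0.3989, so R = 0.1592 / 0.25 = 0.637, a loss of 36%.

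**Tertiles.** The cut-points are ±0.431, with φ = 0.3636. The outer groups have means ±0.3636 / (1/3) = ±1.091 and the middle group has mean 0. R = 2 × (1/3) × 1.091² = 0.793, a loss of 21%.

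**Power of a 1-df test.** The continuous test has expected z = 1.960 + 0.842 = 2.802. After grouping, power = Φ(2.802√R − 1.960).
- Median split: 2.802 × 0.798 = 2.235; Φ(0.275) = 0.61.
- Tertile trend: 2.802 × 0.891 = 2.495; Φ(0.535) = 0.70.

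**Tertiles as an unordered 2-df test.** The noncentrality available is 7.849 × 0.793 = 6.23, which gives 60% power. A 2-df test needs 9.635 for 80% power, against 7.849 on 1 df. The effective sample size retained is 0.793 × 7.849 / 9.635 = 0.646, a loss of 35%.

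| How age enters the test | Loss | Power if continuous age has 80% |
|---|---|---|
| Two groups, 50/50 | 36% | 61% |
| Two groups, 70/30 | 42% | 57% |
| Two groups, 80/20 | 51% | 50% |
| Tertiles, trend | 21% | 70% |
| Tertiles, 2 df | 35% (effective sample size) | 60% |
| Quartiles, trend | 14% | 74% |
| Quintiles, trend | 10% | 76% |

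Trend rows score the groups at their means.

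**Sensitivity to the shape of the age distribution.** With a uniform covariate the loss is 25% for a median split and 11% for tertiles scored as a trend.

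**Dependence on the cut-point.** Moving a two-group boundary from the median to the 80th percentile takes the information retained from 64% to 49%, with the same patients and the same gradient.

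**The case against.** The strongest reply is that the article does not fix the coding of the test. Interactions of covariates with treatment could include a continuous term, and age group may be only a label for display. The number of groups, the cut-points and the coding are usually settled in a statistical analysis plan, which is not shown. This stands in part: the absence of cut-points is no fault, and the loss arises only if the groups enter the test. But the article does choose to name age as a grouped factor and ties the interaction tests to that list, so a clarifying sentence is reasonable.

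Two stronger readings are tempting, and the article supports neither.

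- A reader might infer that a third to a half of the information is lost in each interaction test. That fits two-group splits of a normal covariate between 50/50 and about 80/20. Unordered tests on three to five groups (35% to 41% in effective sample size) also fall in that range. Ordered groups tested for trend lose only 10% to 21%, and a 90/10 split would lose 66%. The article fixes none of these choices.
- A reader might infer that clinical severity is a continuous measure cut into groups, for example ejection fraction, KCCQ-12 or walking distance. The article names none of these as the severity sub-group variable. Its own severity row offers a 0–10 dyspnoea score and an item scheduled only at follow-up. If severity is an ordinal or categorical class, little or nothing is lost.

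The 80% reference power is also hypothetical. The figures describe relative loss, not this trial's actual power for an interaction.

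**Conclusion.** The point holds for age, conditionally on age being grouped in the interaction test. Under rough normality and a roughly linear gradient, the loss is about 36% for a median split, about 21% for tertiles scored as a trend, about 35% in effective sample size for tertiles on 2 df, and 10% to 14% for four or five ordered groups. Under a strongly non-linear gradient the comparison could change, so a spline check is needed.

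For clinical severity the point is conditional on a variable that the article does not define. These are secondary analyses and the primary DAOH conclusion is untouched. Label: cheap improvement.

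**What to change.** In the Data analysis plan (Aim 2), after the sentence on interaction tests, add:

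> *The age-by-treatment interaction will be tested with age as a continuous covariate (linear term), with a spline model as a check for non-linearity. Age groups will be used only to display estimates. If the baseline measure chosen for clinical severity is continuous, it will be handled in the same way; if it is an ordinal or categorical class, it will be tested as such.*

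Sex, region and type of facility stay as they are.

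The cost is one sentence, with no new data for age and no change to the sample size or the primary analysis. The downside is the linearity assumption behind the single-term test, which the spline check is there to expose.
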